Social nurses are registered nurses, that provide support to socially marginalized patients throughout their hospitalization, promote treatment equity, and ensure the best possible treatment outcomes [12–14]. These nurses, who have specialized knowledge and practical experience in working with socially marginalized citizens, originate from positions such as street nurses, shelter nurses, and nurses in substance maintenance treatment clinics.

Previous studies have revealed a strong association between low socioeconomic status (SES) and the presence of COPD [2]. Although individuals from socially marginalized backgrounds tend to have more frequent hospital visits and higher mortality rates [9, 10] there is a lack of available studies examining healthcare utilization, risk factors, and mortality related to COPD in patients in contact with social nurses - a patient group that represents some of the most disadvantaged individuals in Denmark. This gap in knowledge highlights the need for comprehensive investigations to facilitate a more profound understanding of the issue, as that is likely to have significant implications for global healthcare strategies aimed at addressing the multifaceted challenges faced by socially marginalized populations.

We hypothesize that socially marginalized patients in contact with social nurses, have at least a twofold higher prevalence of COPD compared to the general population, as smoking is highly prevalent in lower income groups and is adding to socioeconomic inequalities [15, 16].

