### Study design

This is a prospective longitudinal study with 5 years follow-up from the date of inclusion.

The power calculation is based on the assumption that the prevalence of COPD will be twice the prevalence in the Danish background population (4.3%). With a power of 80% and a significance level of 0.05, a sample comprising 511 patients is required.

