#### Clinical variables

The patients enrolled in this study may be categorized into four groups according to their diagnostic status: those previously diagnosed with COPD (self-reported), those identified as having COPD through screening, those without COPD as determined by screening, and those with an unknown diagnostic status due to insufficient lung function test. COPD identified through screening refers to people whose post-bronchodilator FEV1/FVC ratio is less than 0,7, according to the measurements obtained by the social nurse.

When assessing the prevalence of COPD, the groups diagnosed through screening and self-reported COPD are considered. Participants who are unable to perform spirometry are classified as having an unknown diagnostic status and are not included in the calculation of COPD prevalence.

At the 5-year follow-up, the prevalence of patients diagnosed with COPD after screening is identified either through the National Patient Health registry based on the ICD10 code J.44 or by examining prescriptions for COPD medication (including all types of inhalation medicine) recorded in The Danish National Prescription Database.

The utilization of healthcare services is evaluated based on all hospital contacts, including outpatient visits, admissions, and emergency department (ED) visits.

Admission diagnosis and department will be included as descriptive variables - partly to ascertain whether there are patterns in where the screening has the greatest impact, and partly to assess whether there is selection bias in the study.

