### Statistical considerations

Continuous variables will be presented as mean with standard deviation if the variable can be assumed to be normally distributed, otherwise, the median and interquartile range will be presented. Categorical variables will be presented with frequencies for each level and their corresponding percentages.

The prevalence of COPD in the study population will be compared to the prevalence in the Danish general population using an unadjusted test of the ratio of proportions, with a normal approximation of the logarithm of the ratio.

Since participants can die or otherwise drop out during the follow-up period, participants contribute with different follow-up lengths. The number of contacts in the follow-up period will therefore be reported as a rate (contact rate) of the number of contacts divided by the follow-up length, that is as contacts per year.

The healthcare contact rate will be compared among the three previously described COPD groups: undiagnosed COPD at inclusion who underwent further assessment, undiagnosed COPD without further assessment, and previously diagnosed COPD at inclusion, using a Poisson regression model. The model will include potential confounders as independent variables in addition to the COPD groups.

Sub-analyses for the rate of acute contacts and outpatient contacts will be conducted using models constructed in the same way as for all contacts.

Medication usage as a rate: number of prescriptions per year. Likewise, a Poisson regression model will be used to compare the rates among the COPD groups. However, the groups will be divided into no COPD versus diagnosed COPD. We will employ rigorous control for potential confounders. Specifically, age, smoking history, and comorbidities will be included as covariates in our models.

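### The 511 is the per-group size of a two-sample test, so the stated 80% power is not that of this one-cohort comparison (about 98–99%), and the calculation does not address the twofold hypothesis

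*Protocol article*

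**What the plan says.** Three places in the protocol article bear on this.

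- **Hypothesis** (Introduction, Background and rationale): patients in contact with social nurses "have at least a twofold higher prevalence of COPD compared to the general population".
- **Sample size** (Study design): the assumed prevalence is twice a Danish background prevalence of 4.3%, and "With a power of 80% and a significance level of 0.05, a sample comprising 511 patients is required". No test, sidedness, null ratio or comparator size is given. The same section describes one cohort: "This is a prospective longitudinal study with 5 years follow-up from the date of inclusion".
- **Analysis** (Statistical considerations): "The prevalence of COPD in the study population will be compared to the prevalence in the Danish general population", by an "unadjusted test of the ratio of proportions, with a normal approximation of the logarithm of the ratio". The section does not say whether the general-population prevalence is a constant or an estimate, or which ratio is the null.

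The Clinical variables section adds a point on the denominator: "Participants who are unable to perform spirometry are classified as having an unknown diagnostic status and are not included in the calculation of COPD prevalence".

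**The concern.** The inputs in Study design are enough to identify where 511 comes from, and it comes from a design with two recruited groups. If so, the stated power describes a comparison that the study will not make.

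The second mismatch is between the calculation and the hypothesis. Planning on a ratio of 2 with 80% power means that 2 is the alternative and 1 is the null. The hypothesis is that the ratio is at least 2. A significant test of ratio 1 can occur at an observed ratio well below 2, and nothing in the article says how such a result bears on the twofold claim. Prevalence is the first objective and this is the only comparison with a power statement, so the three passages should fit together before the prevalence results are analysed.

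**Working it through.** **Inputs.** p0 = 0.043, p1 = 2 × 0.043 = 0.086, power 80%, significance level 0.05 and n = 511, all from Study design. Two-sided testing is an assumption (z = 1.960 and 0.8416); it is what reproduces the figure.

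**1. Reproducing 511.** Two-sample pooled test, equal groups, mean proportion (0.043 + 0.086)/2 = 0.0645:

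n per group = [1.960·√(2 × 0.0645 × 0.9355) + 0.8416·√(0.043 × 0.957 + 0.086 × 0.914)]² / 0.043²
= (0.6809 + 0.2912)² / 0.001849 = **511.1**

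With 511 in each of two groups the power is 79.99%. If 511 were the total of two groups, it would be about 51%. Other two-sample versions miss 511: 403 (one-sided), 509 (unpooled), 557 (continuity-corrected), 538 (log ratio). One-sample formulas against a fixed 4.3%, two-sided, give 174 to 334. None gives 511.

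**2. Size for 80% power against a fixed 4.3%, null ratio 1.**

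- Log ratio (the planned test): (1.960 + 0.8416)² × (0.914/0.086) / (ln 2)² = 173.6, so about **174**.
- Score test: [1.960·√(0.043 × 0.957) + 0.8416·√(0.086 × 0.914)]² / 0.043² = 217.1, so 217–218.

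These are normal-approximation sizes. Exact binomial enumeration of the log-ratio test gives 74% power at 174, 77% at 217 and 84% at 256, so the practical requirement is somewhat above the formula value but still far below 511.

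**3. Power at 511 evaluable patients, true prevalence 8.6%, fixed 4.3%.**

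| Test of ratio 1 | Rejects from | Power |
|---|---|---|
| Log ratio, binomial enumeration | 31 cases | 98.7% |
| Exact binomial | 32 cases | 97.9% |
| Score approximation | – | 98.0% |

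The 95% CI half-width at 8.6% is 1.96 × √(0.086 × 0.914/511) = 0.0243, about 2.4 percentage points.

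**4. If the reference is an estimate from N people.** The log-ratio standard error is √[0.914/(511 × 0.086) + 0.957/(N × 0.043)], and power is Φ(ln 2/SE − 1.960).

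| N | Power |
|---|---|
| 511 | 78% |
| 1,000 | 92% |
| 2,000 | 97% |
| 5,000 | 99% |

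Only a reference sample of about 511 brings power near 80%.

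**5. What the test can show about twofold.** The smallest significant result for ratio 1 is 31/511 = 6.07%, a ratio of 0.0607/0.043 = 1.41. Its lower 95% limit is just above 1.00. For the lower limit to exceed 2 (a prevalence of 8.6%), at least 57/511 = 11.15% is needed, a ratio of 2.59. The probability of reaching 57 cases is:

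| True prevalence | Ratio | Probability |
|---|---|---|
| 8.6% | 2.0 | 2.7% |
| 10% | 2.3 | 21% |
| 11% | 2.6 | 48% |
| 12% | 2.8 | 74% |
| 12.3% | 2.9 | 80% |
| 12.9% | 3.0 | 89% |
| 15% | 3.5 | 99.5% |

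**The case against.** The strongest case against the point has four parts.

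- **The reference is not stated to be fixed.** This is correct. A constant 4.3% is an inference from a single cohort and a single quoted figure. The conclusion barely depends on it, because a reference sample of 2,000 or more still gives about 97% power or higher with the planned test. A comparator of 511 would rescue the 80%, but the article describes no such group.
- **The error is conservative.** This also stands. The study is not too small to show a prevalence above 4.3%. Even if only 256 of 511 could be evaluated, the log-ratio test would have about 84% power.
- **Planning on the expected effect against a null of no difference is ordinary practice**, and the formal objective is to investigate and describe prevalence. That is fair. No passage sets a null of ratio 2 or a rule for declaring twofold confirmed, so the article breaks no rule of its own. What remains is that the stated hypothesis has no stated way of being judged.
- **A condensed article may leave test details to the full protocol or SAP.** That excuses the missing sidedness and reference size. It does not excuse a size and power that are stated here and do not fit the comparison stated here.

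A reader might infer that the study has almost no power for its twofold hypothesis. The documents do not support that. The 2.7% is the type I error of a test of ratio 2 when the true ratio is exactly 2, and any test behaves this way at its null boundary. The hypothesis also covers larger ratios, where the probability rises to 74% at a prevalence of 12% and 89% at 12.9%.

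**Conclusion.** The point holds as a mismatch between the sample-size statement, the planned comparison and the hypothesis. The 511 belongs to a two-group design. For this study, 80% understates the power, which is about 98–99% for a test of ratio 1 against a fixed 4.3% with 511 evaluable patients, and 511 is not the number required for 80%. No result is invalidated and no more patients are needed. Separately, a significant test of ratio 1 shows only a prevalence above the background, from an observed ratio of 1.41 upwards, and cannot alone support at least twofold.

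This rests on two-sided 0.05, a true prevalence of 8.6% for the power figures, all 511 evaluable, and a reference that is fixed or drawn from a sample much larger than 511. A reader might also infer that the authors will report any significant ratio as confirming twofold. The article does not say so; it only leaves the matter open.

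**What to change.** Keep 511.

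1. **Study design.** Restate the power for the planned test, for example: with 511 evaluable participants, the log-ratio test (two-sided 0.05, null ratio 1) has about 98–99% power to detect a prevalence of 8.6% against a fixed 4.3%, and the 95% CI half-width is about 2.4 percentage points at 8.6%. If the reference is an estimate, give its sample size, include its variance in the test and recompute the power. If a minimum size for 80% power is quoted, take it from the log-ratio test (about 174 by formula) rather than the score test (217–218), and say that it is an approximation.
2. **Statistical considerations.** State that rejecting ratio 1 shows only a higher prevalence, and that the twofold hypothesis is judged from the confidence interval of the ratio against 2. Note that a lower limit above 2 needs at least 57/511, with about 80% probability at a true prevalence of about 12.3%.

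The cost is wording only, best settled before the prevalence analysis. The downside is a stricter basis for any twofold claim: at a true ratio only slightly above 2, the study will usually show a raised prevalence without establishing that it is at least twofold.

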### Methods

The social nurses are instructed to invite consecutively all eligible patients who fulfill the following inclusion criteria: Patients aged 18 years or older, patients able to comply with study procedures, and patients able to understand Danish.

Recruitment to the study: The social nurse is informed about the admission of an individual socially marginalized patient either by hospital staff, when personally visiting the hospital departments, through telephone or patient record software, by external collaborators (e.g., substance maintenance clinics, shelters, street nurses, etc.), and/or when a patient directly contacts the social nurse.

Social nurses invite all eligible patients to participate in the study. After providing written informed consent, they interview the patients about alcohol and substance use, housing conditions, education, employment, and about respiratory symptoms, especially COPD symptoms (see Supplement for details).

Next, a spirometry is conducted by the social nurse to detect possible obstructive and/or impaired lung function (Fig. 1). It is performed using the NuvoAir device [18] corded to a smartphone/tablet with the app AIR MD. The guidelines recommend that spirometry be performed both before and after the administration of bronchodilator medications. However, due to practical reasons, the study procedure only includes post-bronchodilator spirometry, although it differs from the standard diagnostic practice. A standard dose of short-acting β2-agonist will be administered prior to spirometry.

**Fig. 1 Fig1:**
[figure not shown]
Flowchart indicating the three patient groups with COPD and the process of study-inclusion and 5-year follow-up: (1) undiagnosed COPD at inclusion who underwent further assessment, (2) previously diagnosed with COPD at inclusion, (3) COPD at inclusion who declined further assessment

The app AIR MD algorithm selects the best of three forced expiratory manoeuvres. The app algorithm also informs the nurse about the precision grade and if the result is acceptable.

Participants with identified impaired lung function, that is a FEV1/FVC ratio below 0.7 or the values of FEV1 and/or FVC below 80% of the predicted value, will be referred to the respiratory outpatient clinic at the hospital for further diagnostic work-up. This referral protocol is applicable irrespective of whether the participant has a pre-existing lung condition or not. In cases where it is not feasible for patients to be seen at the respiratory outpatient clinic, they are instructed to contact their general practitioner for subsequent evaluation and management.

Finally, the social nurse asks the patient about their motivation to quit smoking. In addition, they receive information about available options for smoking cessation support, including hospital resources or referrals to cost-free municipal smoking cessation services.

Coordination regarding follow-up assessment, follow-up care, and general support from social nurses constitutes standard care and is not a part of the intervention but should be taken into account in interpreting the findings.

### Outcome measures

From the baseline examination, the study will report the following outcome measures:Prevalence of non-reversible airflow limitation that is a post-bronchodilator FEV1/FVC ration< 0.70Proportion of diagnosed vs. undiagnosed COPD at the time of screening (with a previous diagnosis of COPD defined as a patient-reported diagnosis in the baseline questionnaire)Proportion of patients diagnosed with lung function impairment (FEV1/FVC ratio < 0.7) subsequently examined at a respiratory outpatient clinic/GP within 4 months from screening.Prevalence of patients diagnosed with COPD after screening (identified by ICD10 code J44, or redeemed prescriptions of COPD treatment)Prevalence of participating current smokers who wish to stop smoking (patient-reported outcome in the baseline questionnaire)Prevalence of patients with identified lung function impairment (FEV1/FVC ratio < 0.7) at screening, who have a desire to quit smoking (patient-reported outcome in the baseline questionnaire)Prevalence of patients who want to quit smoking (patient-reported outcome in the baseline questionnaire) and accept the smoking cessation support offers (identified by social nurse notes in patient report).

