### Data collection

#### Baseline

Baseline data are derived from lung function measurements and the interviews and questionnaires completed at inclusion.

The data is sampled online by social nurses using a smartphone or tablet, and the data is directly entered into REDCap (Research Electronic Data Capture) [19]. Further, the results of the spirometry are uploaded directly from the smartphone to REDCap.

If online data entry is not possible, a paper version of the survey will be available. At the end of the inclusion period, they will be sent to the Department of Clinical Research at Hvidovre Hospital and entered manually into REDCap.

Upon reaching the necessary number of participants, the local investigators will refer to the outpatient bookings and physician notes in the electronic patient record, to determine whether the participants underwent further evaluation at a department of respiratory medicine and if a diagnosis of COPD was confirmed (as indicated by ICD10 coding J44).

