## Discussion

Our study is a pragmatic clinical study involving a marginalized patient population that is often excluded from participating in clinical trials due to lower health literacy and marginalization [23].

A potential methodological limitation in this study is the possibility of measurement errors arising from the use of social nurses rather than nurses with specialized respiratory training to conduct spirometry. To mitigate these risks, training is provided through local respiratory medical staff. Additionally, the social nurses are also required to be familiar with the Danish standard for lung function testing [24]. Moreover, social nurses interact directly with five to eight patients during a day shift, based on a subjective assessment of which patients need the most attention. This results in a carefully selected group of marginalized patients, potentially introducing selection bias between the study sites.

Furthermore, the handheld technical equipment used for performing the lung function test may increase the risk of measurement errors. Hence, we cannot make a definite diagnosis of COPD, but detect a possible impairment or obstructive pattern in the spirometric values. When suspicion of lung disease arises, patients undergo the standard diagnostic procedure at the current hospital, with some patients assessed in the outpatient clinic and others referred to their general practitioner. Since we cannot retrieve diagnosis from general practitioners, diagnosis verification is only available for those who attend the outpatient clinic. The five-year follow-up will determine if patients receive regular prescribed medication, facilitating confirmation of the COPD diagnosis.

We employ post-BD spirometry utilizing airflow limitation as the criterion for COPD diagnosis. Although COPD is the predominant cause of irreversible airflow limitation, it is noteworthy that a minority of patients, including those with conditions such as bronchiectasis, cannot be entirely ruled out from our study cohort. Further, an essential consideration involves the exclusion of individuals with severe, acute illnesses from the assessment of COPD prevalence due to their inability to actively participate in lung function measurements.

A strength of the study is the use of a multi-centre design on a national level, which thus with a high degree of validity reflects this subgroup of the Danish population.

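### COPD diagnosed after screening is one label for a baseline outcome, an end-of-recruitment chart look-up and a 5-year register figure, so screening and elapsed time cannot be separated

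*Protocol article*

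**What the plan says.** Four places in the protocol article bear on this outcome.

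- **Outcome measures.** The list opens with "From the baseline examination, the study will report the following outcome measures" and includes "Prevalence of patients diagnosed with COPD after screening (identified by ICD10 code J44, or redeemed prescriptions of COPD treatment"). No window is attached. The item just before it, on attendance for examination, does have one: "subsequently examined at a respiratory outpatient clinic/GP within 4 months from screening".
- **Data collection, Baseline.** "Upon reaching the necessary number of participants, the local investigators will refer to the outpatient bookings and physician notes in the electronic patient record", to see whether participants were evaluated and "if a diagnosis of COPD was confirmed (as indicated by ICD10 coding J44"). Prescriptions are not part of this step. Prescription data first appear under the Five-year follow-up part of Data collection, through register linkage.
- **Variables, Clinical variables.** "At the 5-year follow-up, the prevalence of patients diagnosed with COPD after screening is identified either through the National Patient Health registry" by J44, or "by examining prescriptions for COPD medication (including all types of inhalation medicine").
- **Discussion.** "Since we cannot retrieve diagnosis from general practitioners, diagnosis verification is only available for those who attend the outpatient clinic". It adds that 5-year prescription data will help to confirm the diagnosis.

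The section Five-year follow-up outcome measures does not list this outcome, although Clinical variables places it there.

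**The concern.** The second objective concerns the impact of screening and referral, and this outcome is the diagnostic result of that pathway. In a high-risk cohort, new COPD codes and inhaler prescriptions accumulate with time whether or not anyone was screened. A count of diagnoses after screening can be interpreted only if every participant is observed for the same stated time.

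Three consequences follow from the text as it stands.

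- The baseline report and the 5-year report could give clearly different values under one name, and a reader could not tell which one describes the result of screening.
- The baseline version, which allows redeemed prescriptions, cannot be produced from the data that baseline collection obtains.
- The 5-year outcomes are to be reported by confirmed and non-confirmed COPD diagnosis. If the diagnosis has no date limit, those strata have none either.

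The outcome is also not restricted to participants without a previous COPD diagnosis. Someone already diagnosed or treated before the screen could meet the J44 or prescription criterion without any contribution from it.

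**Working it through.** **The plan's own figure.** The plan gives no number for this outcome. Its sample size of 511 belongs to the comparison of COPD prevalence (4.3% against twice that, 8.6%). The two-sided two-proportion formula, n = [1.960·√(2·0.0645·0.9355) + 0.842·√(0.043·0.957 + 0.086·0.914)]² / 0.043², gives 511.1 per group, so the figure reproduces. This point does not touch it; 511 is used below only as the cohort size.

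**The definitions side by side.**

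| Section | When | Sources |
|---|---|---|
| Outcome measures | baseline report, no window | J44 or redeemed prescription |
| Data collection, Baseline | one look-up when the target number is reached | hospital record, J44 only |
| Clinical variables | 5-year follow-up | register J44 or any inhaled medicine |

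**Observation time at the look-up.** Study setting gives a recruitment start of 19 April 2021 and completion in 2024. Assume a prompt look-up.

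- To 1 January 2024: 987 days / 30.4375 = 32.4 months.
- To 31 December 2024: 1,352 days / 30.4375 = 44.4 months.

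The first recruit therefore has about 32–44 months and the last almost none. If accrual is uniform (an assumption), the share with less than 4 months is 4/44.4 = 9.0% to 4/32.4 = 12.3%, or about 46 to 63 of 511. For them the look-up comes too early even for the plan's own 4-month examination window.

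**Unrelated diagnoses by elapsed time.** The documents give no background rate. Assume a constant rate h of 2%, 5% or 8% per year for a first qualifying code or prescription unrelated to the screen, among people still undiagnosed, ignoring deaths. At a fixed time t the share is 1 − exp(−ht). At one look-up closing uniform recruitment of length T years, the average share is 1 − [1 − exp(−hT)]/(hT).

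| Ascertainment | h = 2% | h = 5% | h = 8% |
|---|---|---|---|
| 4 months | 0.7% | 1.7% | 2.6% |
| 12 months | 2.0% | 4.9% | 7.7% |
| Look-up, T = 32.4/12 = 2.70 | 2.7% | 6.5% | 10.1% |
| Look-up, T = 44.4/12 = 3.70 | 3.6% | 8.7% | 13.4% |
| 5 years | 9.5% | 22.1% | 33.0% |

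The ratio of the 5-year to the 4-month share is 14.3, 13.4 and 12.5. It hardly depends on the rate chosen; the absolute shares do.

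These shares are upper-end illustrations. Deaths remove people from risk, and someone already diagnosed before or through the screen cannot contribute an unrelated first diagnosis.

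**The case against.** The best defence is that the article describes two stages, not a contradiction. General-practice diagnoses cannot be retrieved, so hospital J44 codes are checked first and prescriptions help to confirm the diagnosis at 5 years. On this view the baseline list is simply the content of the first report, no separate third measurement is meant, and what remains is labelling. The look-up date says when records are read, not that events are counted up to that date. Bookings and notes normally carry dates, and exact windows may be left to a fuller document.

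Much of this is fair. Only two ascertainments are described, and the Discussion gives a reason for them. A missing window alone would not be a finding. Three things still stand. The two stages carry the same name. The baseline definition includes prescriptions, which the baseline stage does not collect. And a cut-off applied afterwards can shorten the observation of early recruits but cannot lengthen that of the last ones if records are read when the target is reached.

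A reader might infer more: that the figure depends on elapsed time and not on screening. The documents do not support that. The Methods refer every participant with impaired lung function for work-up, so the figure reflects both, and the defect is that the two cannot be told apart. Nor do the documents support reading 33% as an estimate of bias; it follows from an assumed rate and ignores death. The sample-size outcome, COPD prevalence by screening or self-report, is not affected.

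**Conclusion.** The point holds as an inconsistency in how one descriptive outcome is defined and timed. It is worth correcting before the baseline report, but it does not threaten the powered comparison. The conflict of labels, timing and sources is on the page and needs no assumption. The unequal observation time, almost none to about 32–44 months, follows from the stated recruitment dates and a look-up made promptly on reaching the target.

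The size of the resulting distortion is not known. At an assumed 2–8% per year, unrelated diagnoses would be at most about 0.7–2.6% at 4 months and 9.5–33% at 5 years among those still undiagnosed. What is robust is the contrast: under a constant rate in that range, 5-year ascertainment admits some 12 to 14 times as many unrelated diagnoses as a 4-month window.

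**What to change.** - Define the outcome among participants without a previous COPD diagnosis at baseline.
- Fix one window per participant, counted from the screening date. The 4 months already used for examination is one choice, 12 months another; the documents do not dictate either.
- Do the chart look-up only after the last participant has completed that window.
- Apply the same date cut-off and the same sources to everyone, and state them identically in Outcome measures, Data collection and Clinical variables. Take the prescription component from the register extract, cut at the window.
- Report the 5-year register figure separately, for example as *5-year cumulative COPD diagnosis*, and list it among the 5-year outcomes.

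The cost is wording in three sections and a date cut on records and registers that are already planned. It needs no new data and changes no patient care. The downside is that the baseline figure will be somewhat lower and reported slightly later, since the look-up waits for the last window to close and the prescription component waits for the register extract.
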